### **4.2. Inclusion Criteria**

Subjects must meet all of the following inclusion criteria to be eligible for participation in this study.

1. Subject must have the ability to understand and sign a written informed consent form (ICF), which must be obtained prior to initiation of study procedures.
2. Male or female subject between 18 and 55 years of age, inclusive, at Screening.
3. Subject must be a nonsmoker. The use of nicotine or nicotine-containing products must be discontinued 90 days prior to the first dose of the study drug.
4. Subject must have a calculated body mass index (BMI) from 19 to 35 kg/m^2, inclusive, at study Screening.
5. Estimated glomerular filtration rate (eGFR)  $\geq$  80 mL/min, as calculated by the Modification of Diet in Renal Disease (MDRD) equation as outlined in Section 6.7.6.
6. Subject must have normal liver biochemistry tests: AST, ALT, ALP, and GGT within the normal range. Total bilirubin 1.0 to 1.5 x ULN is permitted in subjects with a medical history of Gilbert's syndrome.
7. Screening laboratory evaluations (hematology, chemistry, and urinalysis) must fall within the normal range of the local laboratory's reference ranges unless the results have been determined by the investigator to have no clinical significance. Note, for Parts B and C, attempts will be made to enroll at least 3 subjects in each cohort with Screening triglycerides  $\geq$  150 mg/dL and/or low-density lipoprotein cholesterol (LDL-C)  $\geq$  130 mg/dL.
8. Subject must have either a normal 12-lead electrocardiogram (ECG) or one with abnormalities that are considered clinically insignificant by the investigator.

9. Females of childbearing potential (as defined in [Appendix 3](#)) must have a negative pregnancy test at Screening and clinic admission.
10. Male subjects and female subjects of childbearing potential who engage in heterosexual intercourse must agree to use protocol-specified method(s) of contraception (as described in [Appendix 3](#)).
11. Male subjects must refrain from sperm donation from clinic admission, throughout the study period, and continuing for at least 90 days following the last dose of the study drug.
12. Female subjects must refrain from egg donation and *in vitro* fertilization from clinic admission, throughout the study period, and continuing for at least 90 days following the last dose of the study drug.
13. Subjects have not donated blood within 56 days of study entry or plasma within 7 days of study entry and must refrain from blood donation from clinic admission, throughout the study period, and continuing for at least 30 days following the last dose of the study drug.
14. Must, in the opinion of the investigator, be in good health based upon medical history and physical examination, including vital signs.
15. Must be willing and able to comply with all study requirements.

#### **4.3. Exclusion Criteria**

Subjects who meet *any* of the following exclusion criteria will not be enrolled in this study.

1. Pregnant or lactating subjects.
2. Subjects with triglycerides  $\geq 500$  mg/dL.
3. Subjects with LDL  $\geq 190$  mg/dL.
4. Subjects who have any serious or active medical or psychiatric illness (including depression) that, in the opinion of the investigator, would interfere with the subject's treatment, assessment, or compliance with the protocol. This would include renal, cardiac, hematological, hepatic, pulmonary (including chronic asthma), endocrine (including diabetes), central nervous, gastrointestinal (including an ulcer or inflammatory bowel disease), vascular, metabolic (thyroid disorders, adrenal disease), immunodeficiency disorders, active infection, or malignancy that are clinically significant or requiring treatment.
5. Subjects who have received any investigational compound within 30 days or 5 half-lives, whichever is longer, prior to study drug dosing.
6. Men who habitually drink greater than 21 units/week of alcohol or women who habitually drink greater than 14 units/week of alcohol (one unit is equivalent to 12 oz/360 mL of beer, a

- 4 oz/120 mL glass of wine, or 1 oz/30 mL of hard liquor); or current alcohol abuse that is judged by the investigator to potentially interfere with the subject's compliance or safety.
7. Positive test for drugs of abuse, including alcohol at Screening or on Admission (Day -1 for SAD cohorts in Parts A and C; Day -2 for MAD cohorts in Parts B and C); or current substance abuse that is judged by the investigator to potentially interfere with the subject's compliance or safety.
  8. A positive test result for human immunodeficiency virus (HIV-1) antibody, hepatitis B (HBV) surface antigen, or hepatitis C (HCV) antibody.
  9. Subjects who have poor venous access that limits phlebotomy.
  10. Subjects who have taken any prescription medications or over-the-counter medications, including herbal products, within 28 days prior to start of study drug dosing, with the exception of vitamins, acetaminophen (paracetamol), ibuprofen, and/or hormonal contraceptive medications.
  11. Subjects who have been treated with systemic steroids, immunosuppressant therapies, or chemotherapeutic agents within 3 months prior to Screening or expected to receive these agents during the study (e.g., corticosteroids, immunoglobulins, and other immune- or cytokine-based therapies).
  12. Medical history of serious skin disease in the opinion of the investigator, such as but not limited to rash, food allergy, eczema, psoriasis, or urticaria.
  13. Medical history of drug sensitivity or drug allergy (such as anaphylaxis or hepatotoxicity).
  14. Known hypersensitivity to the study drugs, their metabolites, or formulation excipients (see Section 5.2.1).
  15. Presence or history of cardiovascular disease, including significant cardiovascular disease (including a history of myocardial infarction based on ECG and/or clinical history), history of cardiac conduction abnormalities (including any history of ventricular tachycardia), congestive heart failure, cardiomyopathy with left ventricular ejection fraction < 40%, a family history of Long QT Syndrome, or unexplained death in an otherwise healthy individual between the ages of 1 and 30 years.
  16. Syncope, palpitations, or unexplained dizziness.
  17. Implanted defibrillator or pacemaker.
  18. Medical history of liver disease, including but not limited to alcoholic liver disease, autoimmune disorders (e.g., primary biliary cholangitis, primary sclerosing cholangitis, autoimmune hepatitis), drug-induced hepatotoxicity, Wilson disease, clinically significant iron overload, or alpha-1-antitrypsin deficiency).

19. Severe peptic ulcer disease, gastroesophageal reflux disease, or other gastric acid hypersecretory conditions.
20. History of medical or surgical treatment that permanently alters intestinal absorption (e.g., gastric or intestinal surgery). *History of cholecystectomy is not exclusionary.*
21. Unable to comply with study requirements or are otherwise believed, by the study investigator, to be inappropriate for study participation for any reason.
22. Subjects who have received vaccination for COVID-19 within 14 days of Admission (Day -1 in SAD cohorts, Day -2 in MAD cohorts).

## **5. STUDY DRUGS**

### **5.1. Randomization, Blinding, and Treatment Codes Access**

#### **5.1.1. Randomization**

It is the responsibility of the investigator to ensure that the subject is eligible for the study prior to enrollment and all enrollment criteria data are appropriately recorded. Subjects will be assigned a Screening number at the time of signing informed consent. Once a subject number has been assigned to a subject, it will not be reassigned to another subject. If necessary, replacement subjects may be enrolled (to compensate for early dropouts) after discussion and approval from the sponsor. A new unique subject number will be assigned to the replacement subject.

At Screening, study subjects will be assigned to Part A, B, or C, followed by assignment to a cohort within their respective part. Following confirmation of study eligibility on Day -1 (SAD cohorts) or Day -2 (MAD cohorts), eligible subjects will be randomized 4:1 to receive TLC-2716 or PTM and will be assigned a subject number. Note, for SAD cohorts in Part A and for any adaptive cohort in Part C evaluating a total daily dose that is higher than has previously been evaluated, two sentinel subjects, one randomized to TLC-2716 and one to PTM, will be evaluated through Day 2 prior to the randomization of the additional eight subjects in each cohort.

A randomization scheme including subject number and treatment assignments will be provided by the Sponsor to the unblinded study pharmacist for storing in a secure location. Blinded study site investigators and staff will not have access to this list. The study pharmacist, or designee, will remain unblinded throughout the study to allow for preparation of study drug.

#### **5.1.2. Blinding**

During the randomized phase, TLC study team and site pharmacist(s) will be unblinded, while the investigational sites, including investigators and the subjects participating in the study will remain blinded. To mitigate the risks of inadvertently releasing the treatment information to the site or subjects, TLC staff will only be provided with the unblinded information when there is a need to access such information for data analysis to support internal decision making. Should TLC staff receive unblinded information unnecessarily, they will keep it confidential and will not communicate the information to the blinded site staff or subjects.

#### **5.1.3. Procedures for Breaking Treatment Codes**

In the event of a medical emergency in which the treatment code must be revealed to provide medical care to the subject, the investigator may obtain treatment assignment for that subject. TLC recommends but does not require that the investigator contact the TLC MM before breaking the blind. Treatment assignment should remain blinded unless that knowledge is necessary to determine subject emergency medical care. The rationale for unblinding must be clearly explained in source documentation, along with the date on which the treatment assignment was

obtained. The investigator is requested to contact the TLC MM promptly in case of any treatment unblinding.

Blinding of study treatment is critical to the integrity of this clinical study and therefore, if a subject's treatment assignment is disclosed to the investigator, the subject will have study treatment discontinued. All subjects will be followed until study completion unless consent to do so is specifically withdrawn by the subject.

## **5.2. Description and Handling of Study Drugs**

### **5.2.1. Formulation**

The TLC-2716 capsules are available in strengths of 0.5 mg, 2 mg, and 5 mg (as free form equivalent). The capsules are opaque, hard hypromellose capsule shells, and are available in white (0.5 mg), rich yellow (2 mg), and Swedish orange (5 mg). In addition to the active ingredient, each capsule contains inactive ingredients, including lactose, microcrystalline cellulose, mannitol, and HPMC E5.

The PTM TLC-2716 capsules are identical in weight, shape, color, and appearance to the corresponding strengths of active TLC-2716 capsules.

### **5.2.2. Packaging and Labeling**

TLC-2716 capsules are packed in white, high-density polyethylene bottles with silica gel desiccant and polyester packing material. Each bottle contains 30 capsules and is capped with a child-resistant polypropylene screw cap containing desiccant fitted with an induction-sealed, aluminum-faced liner. Study drugs to be distributed to study centers shall be labeled to meet all applicable requirements of the FDA and/or other local regulations, as applicable.

### **5.2.3. Storage and Handling**

TLC-2716 capsules and PTM TLC-2716 capsules should be stored at refrigerated temperatures (2-8°C). Storage conditions are specified on the label. Until study drug capsules are dispensed to the subjects, all bottles of study drugs should be stored in a securely locked area, accessible only to authorized site personnel. To ensure stability and proper identification, the drug products should not be stored in a container other than the container in which they were supplied. Consideration should be given to handling, preparation, and disposal through measures that minimize drug contact with the body. Appropriate precautions should be followed to avoid direct eye contact or exposure through inhalation when handling TLC-2716 capsules and PTM TLC-2716 capsules.

## **5.3. Administration of Study Drug**

In Parts A and B, all study treatments will be administered orally at the study center in the morning at approximately the same time each day, within 5 minutes of completing a standardized meal, and with water. The standardized meal should be initiated 30 minutes prior to study drug administration. Except for the water provided with the study drug(s) and water or

beverages with the standardized meal, subjects will be restricted from water consumption from 1 hour before through 2 hours after dosing.

In Part C, study drug may be administered in a fed or fasted state, QD or BID (BID only in MAD cohorts). In the case of QD dosing in fed state, study drug should be administered as in Parts A and B described above. In the case of fasted state or BID dosing, please see Section 5.3.1 for instructions.

### 5.3.1. Fasting and Meals

**Fed State Dosing:** In Parts A and B, after the collection of fasting safety labs, a standardized meal will be provided and all study treatments will be administered in the fed state. Study drug(s) will be administered at approximately the same time each day and within 5 minutes of completing a standardized meal. The meal should be initiated 30 minutes prior to study drug administration. Following study drug administration, subjects will fast until after collection of the 4-hour PK sample on PK assessment days and 2 hours after study drug administration on all other days. On days of PK assessments, other than the water and beverages provided with study drug(s) and with the standardized meal, water, and other fluids will be withheld for 1 hour before until 2 hours after study drug administration. Water may be consumed following the 2-hour post-dose blood draw for the remainder of the collection period.

In Part C, for potential BID dosing in fed state, breakfast will be initiated 30 minutes prior to study drug administration (first daily dose of BID dosing). The second daily dose of BID dosing will be administered 12 hours ( $\pm$  10 minutes) after the morning dose, and approximately 30 minutes after starting an evening snack, which should occur at approximately the same time each day.

**Fasted State:** Prior to collection of fasting safety labs (e.g., fasting serum lipids), as outlined in Table 5 for SAD cohorts and Table 6 for MAD cohorts, subjects are required to conduct an overnight fast (no food or drinks except water) for at least 10 hours prior to sample collection.

**Fasted State Dosing:** In Part C, if applicable, study drug will be administered at approximately the same time each day with water following an overnight fast (no food or drinks except water) for at least 10 hours. Subjects will continue to fast until after the 4-hour PK sample on days of PK sampling and 2 hours after study drug administration on all other days.

Additionally, on PK sampling days, subjects will be restricted from water consumption 1 hour before until 2 hours after dosing, except for the water given with study treatment. A standardized meal will be provided to subjects after the 4-hour post-dose PK blood draw, or as early as 2 hours post-dose on days without post-dose PK sampling.

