Within Part A and SAD cohorts in Part C, initiation of single-dose administration at escalating dose levels will be determined by evaluation of cumulative safety data, and available and relevant PK and PD data up to and including Day 4, following single-dose administration of the previous dosing cohort. Similarly, in MAD cohorts in Parts B and C, initiation of multiple-dose administration at a higher dose level will be determined by evaluation of safety and available PK and PD data from all subjects enrolled through Day 14 of the previous dosing cohort. Additionally, in adaptive cohorts in Part C, sentinel dosing will be utilized in any cohort wherein the total daily dose to be administered is greater than has previously been evaluated. In these multiple-dose cohorts, to support a comprehensive evaluation of the relationship between TLC-2716 PK and PD, all subjects regardless of treatment assignment will be administered placebo capsule(s) on Day -1 to characterize the baseline daily variation of PD markers for subsequent comparison with changes that occur during dosing of TLC-2716 or PTM from Day 1 through 14. Additional details regarding dose escalation criteria are provided in Section 3.2.

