f Symptom driven physical exams will be performed during confinement as needed, based on reported signs and symptoms.

g Hematology: CBC with differential. Collected in fasting state prior to morning meal, if applicable.

- h Serum Chemistry: alkaline phosphatase, AST, ALT, GGT, total bilirubin, direct and indirect bilirubin, total protein, albumin, bicarbonate, BUN, calcium, chloride, creatinine, glucose, phosphorous, magnesium, potassium, sodium, uric acid, and amylase (reflex lipase testing is performed in subjects with total amylase > 1.5 X ULN). Collected in fasting state prior to morning meal, if applicable.
- i Coagulation: INR, PTT. Collected in fasting state prior to morning meal, if applicable.
- j Lipids: total cholesterol, HDL, LDL, TG. Collected in fasting state prior to morning meal, if applicable.
- k On Day 1, to be collected 12 hours post-dose only, with exception of 12-lead ECG which should be 2 hours post-dose.
- l Females of child-bearing potential only (see [Appendix 3](#) for definition).
- m As necessary only for evaluation of post-menopausal state in females of any age with amenorrhea > 12 months at time of Screening (see [Appendix 3](#)).
- n For MAD cohorts, all subjects will receive PTM on Day -1, and study drug starting Day 1.
- o PK sampling will occur relative to the morning dosing of TLC-2716 at the following time points for each cohort:
- Day 1: Pre-dose ( $\leq 10$  minutes prior to dosing), 0.25, 0.5, 1, 1.5, 2, 2.5, 3, 3.5, 4, 6, and 12 hours post-dose
  - Days 3, and 7: Pre-dose ( $\leq 10$  minutes prior to dosing), 2, and 4 hours post-dose
  - Day 14: Pre-dose ( $\leq 10$  minutes prior to dosing), 0.25, 0.5, 1, 1.5, 2, 2.5, 3, 3.5, 4, 6, 12, 24, 48, and 72 hours post-dose
- For any cohorts in Part C with BID administration, see Protocol Section [6.5](#) for details on the timing of PK collections.
- p Collected relative to the morning dosing of TLC-2716 or PTM to measure PD biomarkers for TLC-2716 at the following time points:
- Day -1: (all  $\pm 5$  minutes of Day 1 time points), 0, 2, 4, 6, and 12 hours
  - Day 1, 7, and 14: Pre-dose ( $\leq 10$  minutes prior to dosing), and 2, 4, 6, and 12 hours post-dose
- All post-dose timings are relative to morning dose for once-daily dosing or BID dosing.
- q Collected pre-dose ( $\leq 10$  minutes prior to dosing), and 4 hours post-dose.
- r Collected pre-dose ( $\leq 10$  minutes prior to dosing), 2, 4, 6, and 12 hours post-dose.

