### **MAD Cohorts in Parts B and C:**

Day 1: Pre-dose ( $\leq 10$  minutes prior to dosing), 0.25, 0.5, 1, 1.5, 2, 2.5, 3, 3.5, 4, 6 and 12 hours post-dose

Days 3, and 7: Pre-dose ( $\leq 10$  minutes prior to dosing), 2, and 4 hours post-dose

Day 14: Pre-dose ( $\leq 10$  minutes prior to dosing), 0.25, 0.5, 1, 1.5, 2, 2.5, 3, 3.5, 4, 6, 12, 24, 48, and 72 hours post-dose

***If in any MAD cohort in Part C, BID administration is evaluated, PK assessments should be performed at the following time points.***

Day 1: Pre-dose morning ( $\leq 10$  minutes prior to dosing), 0.25, 0.5, 1, 1.5, 2, 2.5, 3, 3.5, 4, 6, and 12 hours post morning dose (12-hour time point collected prior to evening dose)

Days 3 and 7: Pre-dose morning ( $\leq 10$  minutes prior to dosing), 2, and 4 hours post morning dose

Day 14: Pre-dose morning ( $\leq 10$  minutes prior to dosing), 0.25, 0.5, 1, 1.5, 2, 2.5, 3, 3.5, 4, 6, and 12 hours post morning dose (12-hour time point collected prior to evening dose), 12.5, 13, 14, 16, 18, 24, 48, and 72 hours post-dose

Every effort should be made to collect PK samples at the scheduled time point.

Plasma concentrations of TLC-2716 (and its metabolites, as applicable) will be determined and other PK parameters evaluated, as appropriate. Sampling time points may be modified by the sponsor based on emerging data and assay feasibility.

For all cohorts, a single PK sample will be collected at the ET visit, if applicable.

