#### **6.6.1. Plasma and/or Serum Pharmacodynamic Assessments**

Blood samples will be collected to measure PD biomarkers for TLC-2716 at the time points described below, where '0' indicates the pre-dose time point in the morning. Blood samples for PD assessments will be collected in the same subject order on each day, including the pre-dose

day, in each cohort. For MAD cohorts, the collection times on the day prior to the dosing day (e.g., Day -1) must match those on the days of subsequent dosing ( $\pm 5$  minutes).

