**MAD Cohorts in Parts B and C:**

Day -1: (all  $\pm 5$  minutes of Days 1, 7, and 14 time points), 0, 2, 4, 6, and 12 hours

Days 1, 7, and 14: Pre-dose ( $\leq 10$  minutes prior to dosing), and 2, 4, 6, and 12 hours post-dose

All post-dose timings above are relative to the morning dose for QD or BID dosing. In the case of BID dosing in Part C, the 12 hours post-dose time point must be collected prior to the second daily dose of the study drug.

Sampling time points may be modified by the sponsor based on emerging data and assay feasibility.

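### In MAD cohorts the post-dose meal rule follows PK sampling, so the Day -1 placebo profile is matched to Days 1, 7 and 14 on clock time but not on meals from the 4-hour PD sample onward

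*Combined protocol and SAP*

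**What the plan says.** Protocol Section 5.3.1 ties the length of the post-dose fast to PK sampling. Under fed dosing, subjects "fast until after collection of the 4-hour PK sample on PK assessment days and 2 hours after study drug administration on all other days". The paragraph on fasted dosing in Part C makes the same split: a meal is given after the 4-hour PK draw, "or as early as 2 hours post-dose on days without post-dose PK sampling".

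Section 1.3.1 gives the purpose of Day -1 in MAD cohorts: "all subjects regardless of treatment assignment will be administered placebo capsule(s) on Day -1 to characterize the baseline daily variation of PD markers", for comparison with the dosing days that follow. Section 6.6.1 protects that comparison by clock time: "the collection times on the day prior to the dosing day (e.g., Day -1) must match those on the days of subsequent dosing", within 5 minutes. It also keeps the order of subjects the same on each day. Neither section says anything about matching meals. Section 1.3 nevertheless justifies the inpatient setting partly by the need for a consistent diet, because diet can affect serum lipids.

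**The concern.** Day -1 is useful as a PD comparator only if it differs from Days 1, 7 and 14 in treatment and in little else. The protocol controls the clock closely but lets the meal background depend on whether PK blood is drawn. Because Day -1 has no PK samples, it falls under the shorter fast. The 4-hour and later samples that day can then be taken at a different interval after food than the samples they are paired with, and a within-subject difference would mix a meal effect with a drug effect.

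The endpoints concerned are exploratory. Even so, Section 8.2.1 lets the sponsor use PD data in dose escalation and in designing Part C, and Section 1.3 looks to the study's PD data for Phase 2 dose selection. A mismatched Day -1 profile cannot be collected again once dosing has begun.

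**Working it through.** The plan states no figure on this point, so the check sets the schedules beside the meal rule.

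**Inputs**
- PK days in MAD cohorts: Table 6, footnote o, opens "PK sampling will occur relative to the morning dosing of TLC-2716 at the following time points for each cohort" and lists Days 1, 3, 7 and 14. Day -1 is not listed.
- 4-hour PK sample, from Section 6.5.1: taken on Day 1 ("0.25, 0.5, 1, 1.5, 2, 2.5, 3, 3.5, 4, 6 and 12 hours post-dose"), on Days 3 and 7 ("minutes prior to dosing), 2, and 4 hours post-dose") and on Day 14.
- PD samples, from Section 6.6.1: Day -1 is taken within 5 "minutes of Days 1, 7, and 14 time points), 0, 2, 4, 6, and 12 hours". Days 1, 7 and 14 have pre-dose, 2, 4, 6 and 12 hours. Section 6.6.3 gives exploratory biomarkers the same times.
- Breakfast under fed dosing starts 30 minutes before the dose (Sections 5.3 and 5.3.1).

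**Result of applying the rule (fed QD dosing)**

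| | Day -1 | Days 1, 7 and 14 |
|---|---|---|
| 4-hour PK sample | No | Yes |
| PD sample at 4 h | Yes | Yes |
| Earliest post-dose meal | 2 h | After the 4-h sample |
| At the 4-h PD sample | Up to 4 − 2 = 2 h since a meal | No food since breakfast began, 4 + 0.5 = 4.5 h earlier |
| At the 6-h PD sample | Up to 6 − 2 = 4 h since the earliest permitted meal | At most 6 − 4 = 2 h since it |

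Three of the four PD days share one meal rule and the comparator day has another. In a fasted Part C cohort the gap has the same form, except that on the dosing days the subject has not eaten since before the overnight fast.

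**Does reading Day -1 placebo as something other than study drug help?** Footnote n of Table 6 separates placebo on Day -1 from study drug starting on Day 1. On that reading no post-dose fast is stated for Day -1 at all, so the days remain unmatched.

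**Scope**
- The rule applies to Part B (50 subjects), to Part C QD fed cohorts (through Section 5.3) and to fasted Part C MAD cohorts.
- For Part C fed BID cohorts, Section 5.3.1 states no post-dose fast. The number of Part C subjects covered is therefore not fixed; 50 is only an upper bound.
- Pre-dose PD samples are not touched, nor are lipids from the fasting safety labs, which Section 6.6 places before breakfast (the 12-hour draw on Day 1 excepted).
- NMR LipoProfile and whole-blood samples are not collected on Day -1, so they have no comparator there to mismatch.

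**Size of the effect.** If a meal changes a marker's 4-hour value on Day -1 by a fraction x, a subject with no drug effect shows an apparent change of −x/(1 + x) against Day -1. The documents give neither the size nor the sign of x for any marker, so the calculation stops there.

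**The case against.** The strongest reply is that the planned analyses hardly depend on this comparison.

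- **Lipids.** SAP Section 6 analyses fasting triglycerides and cholesterol fractions, and Protocol Section 6.6 takes serum lipids from safety labs drawn before breakfast, apart from the Day 1 12-hour draw. This stands. A reader might infer that a Day -1 meal would create a false triglyceride reduction resembling a drug effect. The documents do not support that. The synopsis lists triglycerides among the PD biomarkers, so they may be assayed at 4 hours, but no analysis of 4-hour triglycerides is specified and no meal effect is given.
- **Baseline.** SAP Section 9 says only that changes from baseline may be evaluated, and SAP Section 3.7.2 takes baseline by default as the last value before study intervention. A clock-matched Day -1 difference is the design intent of Section 1.3.1, not a specified SAP analysis. This also stands.
- **Concurrent placebo.** Placebo subjects follow the same meal rule on the same days, so a contrast with them is less exposed. But there are 2 per cohort. The PD Analysis Set in Protocol Section 8.3.1.3 requires a dose of TLC-2716, which as worded leaves placebo subjects out, and SAP Section 9 mentions no placebo contrast.
- **Practice at the site.** The unit may hold the Day -1 meal until after 4 hours, in keeping with the aim of a consistent diet. Section 3.1.3 also says that meal conditions in Part C, once chosen, stay constant within a cohort. Neither overrides the explicit split between PK days and other days, and Section 3.1.3 does not reach Part B.

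**Conclusion.** The gap in the text is real. Followed as written, Section 5.3.1 permits a meal between 2 and 4 hours on Day -1 and forbids it on Days 1, 7 and 14. The 4-hour and later PD and exploratory samples can then be matched on time but not on meals, which undermines the comparison described in Section 1.3.1. The difference in permitted meal timing is up to 2 hours, and it applies to each of the three dosing days compared with Day -1.

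This is a cheap improvement to an exploratory comparison; the safety and PK objectives are not in question. The conclusion rests on two conditions: that the site uses the freedom the rule gives, and that someone makes the time-matched Day -1 contrast. It does not establish that any PD result would be biased in a particular direction or by a particular amount.

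**What to change.** In Section 5.3.1, in both the fed and the fasted dosing paragraphs, key the longer fast to *PK or PD assessment days, including Day -1 in MAD cohorts*, and state that post-dose meals are served at the same clock times on Days -1, 1, 7 and 14. Apply the same matching to the fed BID paragraph, which has no post-dose meal rule now. Add a cross-reference in Section 6.6.1 and Table 6 so that the meal schedule sits beside the sampling times.

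The cost is a small wording change and an adjusted site meal schedule. Under the QD fed and fasted rules, confined subjects fast up to 2 hours longer on the placebo day, as they already do on Days 1, 7 and 14.
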